### Power analysis

A power analysis that allows for the conduct of country specific analyses was undertaken. Hill-Briggs [44] found that a literacy adapted diabetes and CVD education intervention among an urban African American population resulted in a change in mean knowledge score from 2.7 ± 1.7 to 4.7 ± 2.0 (maximum score possible = 9) among people with low health literacy. Assuming the proposed intervention will result in small to medium improvements in medication knowledge and health literacy practices, the minimum sample size required at each of the five sites to detect an effect size of 0.4 respectively for mean pre-post test scores with a power (1-β) of 0.8 and alpha of 0.05 is 52. For an effect size of 0.3, 90 patients would be needed. Our recruitment targets are, therefore, 100 participants at each of the two NZ sites, 100 participants in Australia, and 120 at each Canadian site.

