### Eligibility

Patient participants are eligible for the trial if they are Indigenous adults ≥ 20 years of age and are enrolled with the participating health services. In addition they need to have been diagnosed with angina pectoris, myocardial infarction, transient ischaemic attacks or stroke OR (for Canada and Australia only) were known to be at risk of a CVD event and receiving medication to manage this risk. In Australia these participants were eligible if they were at high risk (≥15 % risk of a CVD event in the next five years) [36]. In Canada participants were eligible if they were assessed as having at least internediate risk (≥15 % risk of an event in the next 10 years) [42,43]. Finally, all participants need to be taking at least two of the following types of medicines: a statin, aspirin, a beta blocker, or an ACE inhibitor. Eligible participants will be excluded from the trial if they have a condition which means they are unable to provide informed consent or they have a cognitive deficit that interferes with their ability to participate in the intervention.

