### Intervention

The intervention consists of an educational session delivered by health professionals who will have received training in health literacy, and strategies to support knowledge acquisition and the development of health literacy skills using adult education principles. A booklet, designed by the medical and health literacy research team members, will be provided to participants. It includes information about CVD, and medication use in general (including prescription labels, side effects, keeping medicines safely, taking medicines safely, and interactions). The booklet also contains specific information about the four CVD medication classes (statins, aspirin, beta blockers, and ACE inhibitors) including the scientific and brand names of the medications, what the medication does, how to take it, interactions, side effects, contraindications to taking the medicine, what to do if experiencing a serious side effect, how to know if the treatment is working, and lipid and blood pressure treatment targets.

An interactive tablet application has been developed for use during each session. This tablet ensures that the nurse/educator covers the CVD medication information in a structured way and provides interactive opportunities for the participant. The application also prints out a participant specific pill card with images of their medications. A list of three participant identified questions for use next time they see their health professional is also printed. In the context of the trial the application will also ensure that information is provided in a standardised manner across all sites.

The written resource and tablet information were standardized across all three countries, however images and background graphic design features varied with local Indigenous culture and language being used in each country.

Participants will only cover information about the medication classes they are currently taking. That is, if they are currently taking a statin and an ACE inhibitor they will cover these two medication types but will not receive information about aspirin and beta blockers.

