### Statistical analyses

Descriptive statistics will describe the baseline characteristics of study participants (age, sex, CVD diagnosis, co-morbidities, medications), baseline blood pressure and lipid measures, and the characteristics of the sessions with respect to location (home/office) and whether or not family members were present. Finally we will describe the baseline health literacy skills and practices of participants including how and from where/whom they acquire information CVD medications.

To assess the effect of the intervention on patient knowledge about their medication we will examine the mean knowledge scores for each of the four CVD medication groups over time. We will test changes in mean scores from pre session one (T1) to post session three (T6). Baseline characteristics of participants who enrolled but did not complete the study will be compared to participants who finished the intervention to examine whether drop out was determined by specific characteristics or not.

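### The sample size counts participants per site, but knowledge is analysed per medication class, so the stated 80% power for an effect of 0.3 does not carry over to class-level tests at single sites or in Australia unless nearly everyone takes the class

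*Protocol article*

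**What the plan says.** The Power analysis section opens with "A power analysis that allows for the conduct of country specific analyses was undertaken". It then gives "the minimum sample size required at each of the five sites to detect an effect size of 0.4", "for mean pre-post test scores with a power (1-β) of 0.8 and alpha of 0.05 is 52", and adds "For an effect size of 0.3, 90 patients would be needed". The recruitment targets follow as a consequence: "100 participants at each of the two NZ sites, 100 participants in Australia, and 120 at each Canadian site". That makes 200 in New Zealand, 100 in Australia and 240 in Canada, 540 in all. No allowance for class use or dropout is mentioned.

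Three other sections determine who enters a knowledge test:

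- Eligibility: "all participants need to be taking at least two of the following types of medicines", the list being statin, aspirin, beta blocker and ACE inhibitor.
- Intervention: "Participants will only cover information about the medication classes they are currently taking". The first primary outcome under Main study outcomes is limited in the same way, to a participant's own classes.
- Statistical analyses: "we will examine the mean knowledge scores for each of the four CVD medication groups over time", with the change tested from T1 to T6.

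**The concern.** The sample size and the analysis use different units. The power section counts participants at a site. The analysis section counts, for each class, only the participants who take it. Unless everyone takes all four classes, at least one class test has fewer pairs than the site has participants.

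Medication knowledge is the first-listed primary outcome, and the article commits to country-specific analyses. If class-level power is taken from the stated figures, a non-significant change for a less-used class at one site, or in Australia, could be given more weight as evidence of no effect than the number of users justifies. The article states the sample size, the power and the unit of analysis itself, so the mismatch is within its own text and is not a detail left to another document.

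**Working it through.** **Inputs from the protocol article.** Effects 0.4 and 0.3, power 0.80, alpha 0.05, minimums 52 and 90, targets 100 or 120 per site (Power analysis); at least two of four classes (Eligibility); one mean score per class, T1 to T6 (Statistical analyses).

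**Assumed, because not given.** The share of participants taking each class, the dropout rate, and two-sided testing.

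**Step 1: reproduce the stated figures.** For a paired t-test on the change score with standardised effect d, power is the probability that a noncentral t variable with n − 1 degrees of freedom and noncentrality d√n exceeds the two-sided 5% critical value in absolute size. The smallest n giving 80% power is 52 for d = 0.4 and 90 for d = 0.3, an exact match. The alternatives do not match: a one-sided t-test gives 41 and 71, and a two-sample comparison gives 99 and 175 per group. So 52 and 90 are numbers of people who each contribute one pair to one test.

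**Step 2: number in a class test.** n per class = participants × class share × (1 − loss). The four class shares add up to the mean number of classes per person, which is at least 2. The average share is therefore at least 2/4 = 50%, but a single class can be lower.

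**Step 3: power at the stated minimums, 50% share, no loss.**

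- 52 × 0.5 = 26 users: power 0.50 for d = 0.4.
- 90 × 0.5 = 45 users: power 0.50 for d = 0.3.

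**Step 4: power at the recruitment targets, no loss.**

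| Participants | Class share | Users | Power, d = 0.3 | Power, d = 0.4 |
|---|---|---|---|---|
| 100 (one site; Australia) | 75% | 75 | 0.73 | 0.93 |
| 100 | 50% | 50 | 0.55 | 0.79 |
| 100 | 30% | 30 | 0.36 | 0.56 |
| 120 (one Canadian site) | 75% | 90 | 0.80 | 0.96 |
| 120 | 50% | 60 | 0.63 | 0.86 |
| 120 | 30% | 36 | 0.42 | 0.65 |
| 200 (New Zealand) | 50% | 100 | 0.84 | 0.98 |
| 240 (Canada) | 50% | 120 | 0.90 | 0.99 |

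**Step 5: class share needed for 80% power, no loss.** Divide 52 or 90 by the number of participants.

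| Participants | d = 0.4 | d = 0.3 |
|---|---|---|
| 100 | 52/100 = 52% | 90/100 = 90% |
| 120 | 52/120 = 43% | 90/120 = 75% |
| 200 | 52/200 = 26% | 90/200 = 45% |
| 240 | 52/240 = 22% | 90/240 = 38% |
| 540 | 52/540 = 10% | 90/540 = 17% |

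**Step 6: add an assumed 10% loss, 50% share.** A site of 100 has 100 × 0.5 × 0.9 = 45 users: power 0.50 for d = 0.3 and 0.75 for d = 0.4. A site of 120 has 54 users: 0.58 and 0.82. The effect detectable with 80% power is about 0.43 at 45 users (a 100-person site or Australia), 0.30 at 90 users (New Zealand) and 0.27 at 108 users (Canada).

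**The case against.** The best defence is that nothing was miscalculated and the trial does not stop at the minimums. The targets are about twice 52, so at 50% use the power for 0.4 is 0.79 or 0.86. The power section says it serves analyses by country, the analysis section names no site-level class test, and a test pooled over all 540 needs only about 17% use for an effect of 0.3. Half use is also the lowest average that eligibility allows, reached only if nobody takes three or four classes. Finally, the cited study's change from 2.7 (SD 1.7) to 4.7 (SD 2.0) is far larger than the planned effects: 2.0/√(1.7² + 2.0² − 2r × 1.7 × 2.0) is 0.76 at an assumed pre-post correlation r of 0, and 1.37 at r = 0.7.

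Most of this stands, and it limits the point. A reader might infer that the class-level tests lack 80% power outright, for 0.4 as well as 0.3 and at every level. The documents do not support that, given the targets and the pooled country figures. A reader might also infer that the targets were set against 90. The article derives them after giving both 52 and 90, and 100 is also close to 2 × 52, so the text does not settle it.

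The defence does not remove the mismatch. The minimum is stated for each of the five sites. Australia is one service with 100 participants, so a country-level analysis there gains nothing from pooling. A large effect in another population does not make the stated power for 0.3 correct. And a 50% average still allows an individual class to fall below 50%.

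**Conclusion.** The point holds in a limited form. As written, 52 and 90 per site give 80% power only for a test that every participant enters; for a class that half of them take, power at those numbers is about 50%. At the recruitment targets the clear shortfall is for an effect of 0.3 at single sites and in Australia: at 50% use and no loss, power is 0.55 with 100 participants and 0.63 with 120, and 80% power needs about 90% or 75% class use. The effect of 0.4 is largely kept, and New Zealand and Canada pooled are adequate for 0.3 at 50% use before dropout.

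The size of the shortfall rests on class shares and losses that the article does not report. What needs no such assumption is the mismatch between the unit counted in the power section and the unit analysed.

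**What to change.** In the Power analysis section, restate 52 and 90 as users of a given medication class with both T1 and T6 scores. Give the assumed share of participants on each class and the assumed loss. State the level (site, country or pooled) at which class tests are powered, and the effect detectable there with 80% power. At 50% use and 10% loss, for example, that effect would be about 0.43 for a 100-person site or Australia, 0.30 for New Zealand and 0.27 for Canada.

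Optionally, add a participant-level knowledge score over the classes taken at T1 as an additional analysis. Every participant with T1 and T6 scores contributes to it, so the participant-count calculation applies. Replacing the class-specific analysis with such a score is a separate design choice and is not needed to correct this point.

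The cost is a rewording of the power section, with no extra participants or data. The drawback is that the stated class-level power becomes less favourable.

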### Intervention

The intervention consists of an educational session delivered by health professionals who will have received training in health literacy, and strategies to support knowledge acquisition and the development of health literacy skills using adult education principles. A booklet, designed by the medical and health literacy research team members, will be provided to participants. It includes information about CVD, and medication use in general (including prescription labels, side effects, keeping medicines safely, taking medicines safely, and interactions). The booklet also contains specific information about the four CVD medication classes (statins, aspirin, beta blockers, and ACE inhibitors) including the scientific and brand names of the medications, what the medication does, how to take it, interactions, side effects, contraindications to taking the medicine, what to do if experiencing a serious side effect, how to know if the treatment is working, and lipid and blood pressure treatment targets.

An interactive tablet application has been developed for use during each session. This tablet ensures that the nurse/educator covers the CVD medication information in a structured way and provides interactive opportunities for the participant. The application also prints out a participant specific pill card with images of their medications. A list of three participant identified questions for use next time they see their health professional is also printed. In the context of the trial the application will also ensure that information is provided in a standardised manner across all sites.

The written resource and tablet information were standardized across all three countries, however images and background graphic design features varied with local Indigenous culture and language being used in each country.

Participants will only cover information about the medication classes they are currently taking. That is, if they are currently taking a statin and an ACE inhibitor they will cover these two medication types but will not receive information about aspirin and beta blockers.

The education session will be delivered on three occasions at intervals determined using adult education principles to optimise learning opportunities. The second session is scheduled to occur seven days after the first but can be completed up to two weeks after the scheduled date. The third session is scheduled to occur 28 days after the first session but can be completed up to four weeks after the scheduled date.

The time required to complete each session will vary depending on the number of medications the participant is taking. We anticipate that each session will be no less than 30 minutes and no more than 75 minutes.

Training for research staff will be provided in New Zealand (NZ and Australian research staff) and in Canada. Training sessions with research staff from all three countries will also be undertaken using teleconferences and Skype. Training will be provided in health literacy, principles of adult learning, the delivery of the intervention, and all trial protocols and processes including data collection and quality assurance processes. A detailed training manual will be provided. Training in use of the medication knowledge outcome measures will include the use of standardized scenarios that will be pre-scored by two investigators (SC, SR). Each nurse/educator will score the scenario using the relevant medication knowledge outcomes measures. This process will continue with supplementary training where needed until accuracy and cross-site concordance in scoring is reached. To evaluate scoring practices during the trial this process will be repeated at regular intervals using standardized video scenarios.

### Main study outcomes

The primary study outcome measures will assess changes from baseline to data collection time points for: (1) patient knowledge about the CVD medication classes they are taking; (2) patient knowledge of their treatment targets for lipids and blood pressure; and (3) the use of participant-specified questions with their usual healthcare provider. Secondary outcomes measures will examine changes in patient health literacy skills and practices. Table 1 describes the data collected at the measurement points.

**Table 1 T1:** Summary of trial contacts and data collection

**Time point**		**Measurement**
Enrolment visit.	T0	Consent and enrolment in study. In Canada baseline demographic and clinical information was also collected at this visit
Session one.	T1	Baseline demographic and clinical information (NZ, Australia)
		Pre-session one medication knowledge and health literacy practices
	T2	Post session one medication knowledge and health literacy practices
Session two.	T3	Pre session two medication knowledge and health literacy practices
Seven days after session one.		Health literacy practices between sessions one and two
	T4	Post session two medication knowledge and health literacy practices
Session three.	T5	Pre session three medication knowledge and health literacy practices
28 days after session one.		Health literacy practices between sessions two and three
	T6	Post session three medication knowledge and health literacy practices

### Measurement instruments

Baseline demographic, medical history, medication information, blood pressure and lipid recordings will be collected at the enrolment session or at the start of the first session (T0 or T1 in Table 1). Outcome assessment tools that assess patient knowledge of the scientific and brand name of their medications, class of drug, function of drug, important side effects, special instructions for taking the medicine, and (where relevant) knowledge of lipid and BP treatment targets have been developed for statin, aspirin, beta blockers and ACE inhibitors and will be completed immediately before and after each education session (T1-T6).

Participants’ health literacy skills and practices during each outcome assessment will be assessed (T1-T6). Participants will be asked about their health literacy practices prior to the first session and between each session (T0/T1, T3 and T5). Participants will be asked about their use of their questions for health professionals at the beginning of the second and third sessions (T3 and T5).

### Statistical analyses

Descriptive statistics will describe the baseline characteristics of study participants (age, sex, CVD diagnosis, co-morbidities, medications), baseline blood pressure and lipid measures, and the characteristics of the sessions with respect to location (home/office) and whether or not family members were present. Finally we will describe the baseline health literacy skills and practices of participants including how and from where/whom they acquire information CVD medications.

To assess the effect of the intervention on patient knowledge about their medication we will examine the mean knowledge scores for each of the four CVD medication groups over time. We will test changes in mean scores from pre session one (T1) to post session three (T6). Baseline characteristics of participants who enrolled but did not complete the study will be compared to participants who finished the intervention to examine whether drop out was determined by specific characteristics or not.

## Discussion

In all three countries data obtained in the developmental phase showed significant gaps in patients’ cardiovascular medication knowledge that are likely to interfere with safe and effective medication use. Improving health literacy about CVD medications is one of a range of strategies necessary to reduce the inequitable burden of cardiovascular disease experienced by Indigenous populations. This study will determine if health professional delivered, health literacy oriented educational sessions delivered in the primary care setting enhances medication knowledge and health literacy practices within Indigenous communities in Australia, Canada and New Zealand. If successful the intervention may also be useful for a wider range of medications associated with other long-term conditions and in non-Indigenous contexts.

The study is one of the first international clinical trials conducted solely among Indigenous populations. Building on previously published work about Indigenous involvement in clinical trials [45] the protocol illustrates the application of Indigenous health research principles and protocols [46], such as Indigenous involvement across all roles and throughout the entire project, to clinical trials. Implementation of these principles and processes requires appropriate relationships and communication with the health services, their staff and the study participants. The use of outcomes measures that assess the development of knowledge, skills and practices is informed by Indigenous preferences for strength-based rather than deficit focused research. This strength-based approach is also consistent with Nutbeam’s [30] approach to health literacy.

The study design also illustrates one approach to implementing clinical trials in distinctive local contexts. In Canada, networks of friends and family have been identified by members of our research team as the most important source of health information in diverse local Indigenous communities [47]. Furthermore, the relatively small population sizes of these communities means that, in order to have a sufficient sample to assess the effect of the intervention, it will have to be delivered to all eligible people in the health services. The study design needs to accommodate both these challenges, making a single arm, pre-post design with case studies of the surrounding environments for factors that may influence the effect of the trial, the most suitable design. Similar challenges may be encountered in other studies that are located in relatively small, local populations.

A key audience for our study results will be the Indigenous health service providers who are responsible for providing care to the patients in the study. We will work with these health service provider partners to interpret the study findings and identify recommendations for their practice. We will also share our study findings more broadly with Indigenous and non-Indigenous health policy makers, practitioners, and researchers.
